### Data source

Workstream 1: Routinely recorded electronic patient record data from all admissions to NHS neonatal units in England and Wales, held within the National Neonatal Research Database (NNRD). Data are entered by clinical staff at the point of care and extracted, anonymised and combined by the Neonatal Data Analysis Unit at Imperial College, London. The NNRD has NHS Research Ethics Committee approval (10/80803/151) and approval from the Caldicott Guardians of NHS trusts for research use.

Workstream 2: Quantitative and qualitative data from a variety of sources: questionnaires with parents and healthcare professionals (HCPs); semistructured one-to-one interviews with parents and HCPs; NNRD data, supplemented with data directly from paper-based and electronic patient notes, collected using an electronic case report form, for data items not available within the NNRD; data from EMNODN units on cot capacity, staffing levels and facilities.

Questionnaires will be completed electronically using an online survey platform, with paper copies available should participants request them. Any data from questionnaires completed on paper will be manually digitised, with a sample (10%) checked for verification of data entry. Audio recordings of interviews will be transcribed verbatim and transcripts will be checked against audio recordings to ensure they are accurate and that any identifiable information discussed during interviews is anonymised.

### Eligibility criteria

For workstream 1, we will include infants who: were born at <32 weeks’ GA; survived at least 48 hours from birth; and were admitted for neonatal care from 1 January 2016 to 30 September 2023 to a neonatal unit contributing data to the NNRD. In line with previous work,^18 19^ we will exclude infants with missing data on key characteristics (eg, sex, GA, final discharge destination) as well as infants admitted >12 hours after birth and those missing data for one or more episodes of care.

For workstream 2, we will include parents of infants who: are admitted to one of the 11 EMNODN neonatal units in a 6-month period after implementation of the care bundle; are born at <32 weeks’ GA; and survived at least 48 hours from birth. All eligible parents will be invited to respond to the questionnaires. For the interviews, parents will be purposively sampled to include: parents from different neonatal units; parents of extremely preterm infants (born at 22–27 weeks’ GA) and very preterm infants (born at 28–32 weeks’ GA); parents whose infants received own mother’s milk, mixed feeding or did not receive any own mothers’ milk; parents of infants who had suspected or confirmed NEC; and parents representing different maternal (eg, education) and environmental (including socioeconomic) factors.

We will recruit HCPs working in EMNODN neonatal units. All HCPs will be invited to respond to the questionnaires and some will be purposely sampled to include a range of individuals representing different job roles (unit leads, consultants, junior doctors, nurse practitioners, nurses, healthcare assistants and allied health professionals including dietitians, speech and language therapists) and hospital sites.

All questionnaire respondents and interview participants will provide written informed consent for their participation and use of the data provided, including deidentified direct quotations in study outputs.

### Intervention

The NEC care bundle, designed by a multidisciplinary team, consists of recommendations for neonatal units, alongside parent-facing information, to promote own mother’s milk feeding and ensure optimum nutritional care of preterm infants. A schematic representation of the care bundle is shown in figure 1, giving an overview of an infant’s journey through neonatal care and opportunities to reduce the risk of NEC.

**Figure 1 F1:**
[figure not shown]
Overview of the East Midlands Neonatal Operational Delivery Network (EMNODN) necrotising enterocolitis (NEC) care bundle.

Recommendations to optimise nutritional care include guidance on: ensuring early and adequate parenteral nutrition given when infants cannot have sufficient milk feeds such as in the first hours after birth, while building milk feeds and when unwell (following established National Institute for Health and Care Excellence guidelines^20^); use of oropharyngeal colostrum^21^ (the practice of giving own mothers’ first milk directly into the infant’s oropharynx to enhance immunity and protect against NEC); optimal time and speed of increasing milk feeds^22^; and use of other interventions such as human donor milk,^23^ probiotics^24^ and breastmilk fortifiers.^25^

#### Primary outcomes

Receiving any own mother’s milk at discharge (exclusively or in combination with infant formula).Receiving any own mother’s milk on day 14 of life (exclusively or in combination with infant formula).Severe NEC requiring surgery or resulting in death.^26^

#### Secondary outcomes

Exclusive feeding with own mother’s milk at discharge.Any NEC, including NEC not requiring surgery and not resulting in death.

### Data analysis strategy: workstream 1

After data cleaning, the number of infants with missing data across key variables will be tabulated and the total number of exclusions and final study population size determined. Descriptive statistics will be presented to summarise the distribution of baseline variables during each of the three study phases, separately for the EMNODN units (intervention group) and all other units in England and Wales (control group). Continuous variables will be reported with means and SDs, if shown to be normally distributed using a combined skewness and kurtosis test, or otherwise will be reported using medians and IQRs. Categorical variables will be reported with frequencies and percentages. P values for differences between the three time periods will be reported using the χ^2^ test or the Wilcoxon rank-sum test, as appropriate.

We will use ITS analysis to assess the impact of implementation of the care bundle on the outcomes listed above, as has been used previously in neonatal research.^27^ This is a strong quasiexperimental design which accounts for underlying trends in an outcome. If, for example, rates of NEC were already in decline prior to the implementation of the bundle, the ITS methodology will detect any additional impact of the bundle, above the background decline. It can also account for the impact of any other interventions or changes in population characteristics which might themselves impact outcomes.

We will aggregate outcomes by month of birth (or by 2-month period if necessary to improve statistical power, without detriment to interpretation of results) and plot time series graphs to show the number of cases of each outcome per month over the study period in the EMNODN units combined. We will use a quasi-Poisson generalised additive mixed model^28^ to estimate an incidence rate ratio (IRR) for changes in the incidence of the outcomes in EMNODN units during the evaluation phase, relative to the pre-implementation period. Data for the 4-month implementation phase will be plotted graphically but excluded from statistical modelling as this period is too short to be able to model changes in incidence compared with the pre-implementation period. We will similarly plot and model data for infants admitted to units in the control group, to assess whether there are any changes in the IRR to exclude confounding due to other events or interventions which occurred around the time that the care bundle was introduced.

We will incorporate several covariates into our models as follows:

The total number of admissions per month will be used as an offset term in each model to account for variations in the number of babies ‘at risk’ of the outcomes.The secular trend in each outcome will be captured using a continuous variable coded from 1 to 93 (the total number of months of data across the study period).To assess whether there was a step change in the outcomes, we will include a binary variable coded as 0 during the pre-implementation phase and 1 during the evaluation phase.To assess whether there was any change in trend (upwards or downwards) in the outcomes, we will include a binary variable coded as 0 during the pre-implementation phase and from 1 to 9 (the number of months in the evaluation phase) during the evaluation phase. We will also assess whether there are any quadratic or cubic trends in the outcomes in the evaluation period, though the relatively short (9 months) length of this evaluation period will limit the ability to detect any non-linear trends. We will use the Akaike information criterion (AIC) to compare models with linear, quadratic and cubic trends in the evaluation period, with a smaller AIC indicating better model fit.Month of the year will be included as a cyclic cubic spline to capture any non-linear, seasonal patterns in outcomes, such as the impact of activities related to the annual World NEC Awareness Day^29^ and International Kangaroo Care Awareness Day^30^ (both held annually in May), or any variation in NEC incidence related to seasonality of circulating pathogens.^31^
To account for any potential impact of the COVID-19 pandemic, we will include a binary variable coded as 1 during periods of national ‘lockdown’ and 0 otherwise, in line with our previous work examining the impact of pandemic-related visitor restrictions on own mother’s milk feeding.^32^
ITS studies are not usually affected by confounders relating to population characteristics as these do not typically change significantly over time.^33^ If the characteristics of infants born during each of the three study time periods differ, we will include covariates to capture any differences in potential confounders by month of birth, such as: median GA; percentage of male admissions; median birth weight; percentage of infants with a high-risk NMR-2000 score (a validated score of in-hospital mortality risk)^34^; percentage of infants with a major congenital anomaly; and median length of stay.Plots of the autocorrelation function and partial autocorrelation function will be examined to identify plausible values of the autoregressive (AR) and/or moving average (MA) terms to capture autocorrelation between data points. We will use the AIC to compare models with different plausible values of AR and MA terms, with a smaller AIC indicating better model fit.

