**Trial registration number:**

NCT05934123.

Strengths and limitations of this studyUse of data from the National Neonatal Research Database allows comparison of all infants admitted to neonatal units in the East Midlands with a control group of all infants admitted to units elsewhere in England and Wales.Interrupted time series analysis will allow any changes in own mother’s milk feeding and the incidence of necrotising enterocolitis (NEC) related to implementation of the care bundle to be identified over and above any underlying changing trends.The parallel mixed methods process evaluation will allow us to unpack the ‘how’ and ‘why’ underpinning the results of the interrupted time series analysis.Analysis of routine data will allow all eligible infants to participate without risk of under-recruitment from underserved groups. In the process evaluation, we will purposively seek to include parents from underserved groups who traditionally hesitate to participate in research.NEC is a rare occurrence and so statistical power to detect small changes in incidence related to implementation of the care bundle may be limited.

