### Objectives

Our study comprises two parallel, integrated workstreams with the following objectives:

Workstream 1: Estimate the effects of implementation of the NEC care bundle on rates of own mother’s milk feeding and incidence of NEC, comparing infants admitted to the 11 EMNODN neonatal units with admissions to all other units in England and Wales. We will also describe feeding practices before and after implementation of the care bundle and examine the infant, maternal and unit-level characteristics associated with own mother’s milk feeding and NEC.

Workstream 2: In a multicentre, mixed methods process evaluation in the 11 EMNODN neonatal units, evaluate how well the care bundle was implemented, understand barriers and facilitators to implementation and understand which components contributed most to effectiveness.

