#### Secondary analyses

In addition to the ITS analysis, we will use multivariable logistic regression to conduct a conventional before-after comparison of the odds of each primary and secondary outcome, adjusted for a range of potential confounders measured at the level of the infant, mother and unit. We will include data from both EMNODN and control units and assess whether there is any effect modification by study group. We will use a robust variance estimator to account for the clustering of infants within units and by mother.

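### The primary interrupted time series models EMNODN and control units separately, so it gives no effect estimate net of concurrent national change; the between-group comparison is formally made only in a secondary before-after model

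*Protocol article*

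**What the plan says.** Protocol article, Objectives: workstream 1 estimates the bundle's effects by "comparing infants admitted to the 11 EMNODN neonatal units with admissions to all other units in England and Wales". The strengths and limitations box says that the database "allows comparison of all infants admitted to neonatal units in the East Midlands with a control group of all infants admitted to units elsewhere".

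Data analysis strategy: workstream 1 defines the ITS estimate as an IRR for "changes in the incidence of the outcomes in EMNODN units during the evaluation phase, relative to the pre-implementation period". For the controls it says "We will similarly plot and model data for infants admitted to units in the control group", and gives the purpose: "to assess whether there are any changes in the IRR to exclude confounding due to other events or interventions".

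The listed model terms are the admissions offset, a linear secular trend, a step ("a binary variable coded as 0 during the pre-implementation phase and 1 during the evaluation phase"), a change in slope, season, lockdown, case mix if it differs between periods, and autoregressive or moving-average terms. No study-group term and no group interaction is listed. Nothing says what follows if the control IRR also changes.

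Secondary analyses: an infant-level logistic before-after model will "include data from both EMNODN and control units and assess whether there is any effect modification by study group", with robust variance for clustering. No secular trend is described for it.

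**The concern.** A single-group ITS removes the trend that existed before the bundle. It does not remove a new change that begins at about the same time. A national shift in milk feeding or NEC from late 2022 would enter the EMNODN step or slope in full and be read as an effect of the bundle. The control series is there to deal with this, but fitting it separately and inspecting it has two limits.

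- Two IRRs side by side do not test their difference, and they give no confidence interval for the bundle's effect net of national change.
- If the control IRR moves, the plan offers no corrected estimate. If it does not move significantly, confounding has not been excluded.

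The Discussion says that the results will help decide whether the bundle should be rolled out nationally. That decision needs an estimate that separates the bundle from what happened everywhere.

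**Working it through.** **Inputs from the Protocol article.** There are 80 pre-implementation months (January 2016 to August 2022) and 9 evaluation months (January to September 2023); the 4 implementation months are excluded. For own mother's milk at discharge, baseline prevalence is about 55% with about 23 infants per month. Read as events, this implies 23/0.55 = 41.8 admissions per month. The NEC figures (3/0.07 = 42.9) and the 2022 count (476/12 = 39.7) agree with that reading.

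**Assumptions.** Control volume is not given. I take 10 times EMNODN, with a range of 5 to 20 times. The test is two-sided at 0.05 with no autocorrelation. Dispersion is φ = 1 (Poisson) or φ = 1 − 0.55 = 0.45 (binomial). The second is what a quasi-Poisson fit would tend to estimate if there is no extra month-to-month variation. The size of the shared shock is hypothetical; the document reports none.

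**The plan's own figures.** The only ITS figures given are EMNODN-only power: 80% for +15 points and about 90% for +20 points. A step-only Poisson model (linear trend, two seasonal harmonics) gives 82.9% and 96.8%. With the slope term it gives 35% and 55% (66% and 88% with binomial variance). No variant tried reproduces both stated figures. Alpha, dispersion and method are not stated, so I do not call them wrong, and this point does not turn on them. No power figure is given for a contrast with controls.

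**Shared 5-point rise, no bundle effect.** The EMNODN IRR is expected at 0.60/0.55 = 1.09. The step's standard error (SE) is that of the log IRR. The rejection probability is Φ(δ/SE − 1.96) + Φ(−δ/SE − 1.96), with δ = ln(1.091) = 0.087.

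| Model | φ | SE, EMNODN | EMNODN step significant | Control (10×) step significant |
|---|---|---|---|---|
| Step only | 1 | 0.087 | 17% | 89% |
| Step only | 0.45 | 0.058 | 32% | >99% |
| With planned slope term | 1 | 0.162 | 8% | 40% |
| With planned slope term | 0.45 | 0.108 | 13% | 72% |

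Simulations with binomial outcomes agree: about 30% step-only and about 12-14% with the slope term. If Bonferroni covers the five listed outcomes (0.05/5 = 0.01), the slope-term figure falls to about 4%. The bias in the IRR itself is the same in every row.

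With the planned slope term, the control check therefore misses this shock in about a quarter of cases (binomial variance) to 60% (Poisson variance).

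**Joint model, same scenario.** The ratio of IRRs is expected at 1.09/1.09 = 1.00 and rejects in about 5%.

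**Precision cost.** SE(log ratio) = √(SE²_EMNODN + SE²_control). With equal event rates and a control 10 times as large, this inflates the SE by √(1 + 1/10) = 1.049. For +15 points (step-only, φ = 1, control at 60% and unchanged) the SE goes from 0.083 to 0.087. Power goes from 82.9% to 79.1%, with a range of 75.3% to 81.0% for a control 5 to 20 times EMNODN. For +20 points it goes from 96.8% to 95.2% (93.3% to 96.0%).

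**The case against.** The strongest reply is that the comparison is planned. A reader might infer that the comparison named in the objective is never made. The document does not support that: the secondary logistic model puts both groups together for every primary and secondary outcome and will "assess whether there is any effect modification by study group", with confounder adjustment and clustered variance. The objective also covers all of workstream 1, not the ITS alone. Nor is the control series ignored. It is modelled for exactly this threat, and a large control group makes that check more sensitive.

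A reader might also take 30% as the false-positive rate of the planned analysis. It is not. It comes from an assumed shock in a step-only model that leaves out the planned slope term, the Bonferroni correction and the control check. A significant EMNODN step together with a non-significant control step, which is the pattern that would mislead under the plan, is much rarer. With the slope term it occurs in about 4% of cases by the table (0.126 × 0.282, binomial variance) and about 5-6% in simulation.

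The joint model has limits of its own. It assumes that both groups share concurrent shocks. Baselines differ (55% against about 60% for milk at discharge; 7% against about 5% for NEC). The Introduction reports a milk-feeding bundle in another region, and the Discussion cites national encouragement of local quality improvement. Initiatives in control units could dilute a ratio of IRRs.

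A fuller analysis plan might say how the two models are to be contrasted. But the article does more than leave this open: it fixes the estimate as within-EMNODN and the control model as a check.

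What stands: the secondary model is on the odds scale and describes no trend, so it does not supply the ITS comparison. The check returns no adjusted estimate whether or not it flags a change.

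**Conclusion.** The point holds for the primary ITS, not for the plan as a whole. As specified, the ITS yields an EMNODN IRR that carries any concurrent national change in full, plus a control IRR to be looked at beside it. It yields no estimate or confidence interval for the difference. Formal comparison is left to a secondary analysis without the trend structure that is the reason for using ITS.

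The size depends on a shock that the document does not report. Under an assumed shared 5-point rise with no bundle effect, the EMNODN IRR is about 1.09 against 1.00 for the ratio of IRRs. False positives on the step at 0.05 are about 30% step-only and about 12% with the planned slope term, and lower after Bonferroni. The direction of the bias does not depend on these assumptions. An unchanged control IRR would be reassuring, but it would not justify the claim that confounding had been excluded.

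**What to change.** Fit one controlled ITS to both monthly series, with group, time, group × time, step, slope, group × step and group × slope, keeping the planned offset, seasonal, lockdown, case-mix and autocorrelation terms. For each outcome, report the ratio of IRRs (EMNODN to control) with its confidence interval as the comparative effect on which conclusions about the bundle rest. Say whether it refers to the step or to step and slope together at a named month. Report the EMNODN-only IRR alongside it. Replace the stated aim of excluding confounding with wording that the control series is used to assess and adjust for shared concurrent change.

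The cost is one additional model on data already requested and a short change of wording. The SE is about 4-5% larger if the control series is 10 times EMNODN. Over 5 to 20 times, the loss is about 2 to 8 points of power at +15 points in the step-only calculation. The shared-shock assumption should be stated, and known milk-feeding or NEC initiatives in control units should be noted as a possible source of dilution.

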### Sample size calculation

Workstream 1: The ITS analysis will have approximately 90% power to detect an absolute increase of 20% in the prevalence of receiving own mother’s milk at discharge and 80% power to detect a 15% absolute increase (baseline prevalence approximately 55%, approximately 23 infants per month in the EMNODN from 2017 to 2019; national average c.60%). This target is comparable to the prevalence of own mother’s milk feeding in the best performing neonatal network—in 2021, the South London Neonatal Operational Delivery Network achieved a prevalence of 76% (range by unit 71–80%) of infants receiving own mother’s milk at discharge.^37^ In 21 neonatal units in the UK in 2021, over 75% of infants received own mother’s milk at discharge, with the highest performing unit achieving 86% prevalence.^37^

NEC is a rare occurrence (incidence approximately 7%, approximately 3 cases per month in the EMNODN from 2017 to 2019; national average c.5%), and there is also considerable monthly variability in incidence. Therefore, statistical power to detect small changes in the incidence of NEC will be more limited; we will be powered to detect approximately a two-thirds reduction in the incidence of NEC. In line with previous studies of less common neonatal outcomes,^27^ the point estimate will, however, give an indication of the effect of the care bundle, even if the CI around this point estimate crosses the null value.

Workstream 2: We aim to conduct 33 interviews with parents (either individuals or couples, 3 per EMNODN unit) and 33 interviews with HCPs (3 per unit) using a combination of convenience (self-selecting) and purposeful sampling approaches, the latter particularly to approach parents from underserved groups who usually hesitate to participate in research. These numbers are based on principles of maximum variation and theoretical data saturation, which is related to the sampling approach rather than the analysis.^38^ Preliminary analysis will inform whether we need to use a second strategy based on the notion of inductive thematic saturation^39^ and, in which case, we may need to conduct additional interviews.

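### AIC is undefined for the quasi-Poisson model it is meant to select, and if it chooses the trend shape behind the reported step effect, that test's 5% error becomes about 7–11%

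*Protocol article*

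**What the plan says.** All of this is in the protocol article, under Data analysis strategy: workstream 1, unless another section is named.

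- **Model family.** "We will use a quasi-Poisson generalised additive mixed model".
- **Effect terms.** A step: "To assess whether there was a step change in the outcomes, we will include a binary variable coded as 0 during the pre-implementation phase", and 1 afterwards. A slope change: 0 before, then "from 1 to 9 (the number of months in the evaluation phase) during the evaluation phase".
- **Shape of the evaluation-period trend.** "We will use the Akaike information criterion (AIC) to compare models with linear, quadratic and cubic trends in the evaluation period", with the smaller value taken as the better fit. The text concedes that nine months limits the detection of non-linear trends. It names no default shape.
- **Autocorrelation.** "We will use the AIC to compare models with different plausible values of AR and MA terms".
- **Series.** The secular trend is a "continuous variable coded from 1 to 93 (the total number of months of data across the study period"), but "Data for the 4-month implementation phase will be plotted graphically but excluded from statistical modelling".
- **Multiplicity (Multiple testing).** The incidence rate ratios for primary and secondary outcomes carry 95% confidence intervals and Bonferroni-corrected p values. Selection of the model is not mentioned.

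**The concern.** There are two separate problems.

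First, the criterion does not fit the model. Quasi-Poisson specifies a mean and a variance proportional to it, and nothing more. AIC needs a maximised likelihood, and here there is none. If the mixed model is fitted by penalised quasi-likelihood, software may print an AIC, but it belongs to a Gaussian working model whose pseudo-data change with every fit. Values from different fits are therefore not comparable. Two analysts following the text could adopt different substitutes and select different models.

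Second, selection affects inference. With step, linear, quadratic and cubic terms, up to four parameters describe nine points. A curve chosen because it fits those points also moves the step estimate, which is an intercept extrapolated to just before the first evaluation month. If the step is then tested as though the shape had been fixed, the confidence interval and p value ignore the choice. The step is one of the two terms carrying the effect on all three primary outcomes, and the Discussion says the results will inform whether the bundle is rolled out nationally.

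**Working it through.** **Plan's own figure.** The article gives no type I error for the step after selection. The nearest figure is the power statement in Sample size calculation, which gives neither method nor variance. No single model variant tried reproduced both of its figures, and this point does not depend on them.

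**Inputs from the article.**
- Months modelled: 93 − 4 = 89, of which 80 are before (January 2016 to August 2022) and 9 after.
- Feeding: "baseline prevalence approximately 55%, approximately 23 infants per month in the EMNODN from 2017 to 2019", so 23 / 0.55 ≈ 42 infants a month.
- NEC: about 7% and 3 cases a month, so 3 / 0.07 ≈ 43 infants a month.

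**Assumptions.** 42 admissions a month; a constant rate (no effect); severe NEC at 3% (no rate is given); dispersion 0.45 to 1.9; assumed lockdown months; two seasonal harmonics in place of the cyclic spline; and the lowest-criterion model supplying the step test.

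**Criteria compared.**
- The model specifies E(Y) = μ and Var(Y) = φμ.
- AIC = −2 log L + 2k, which needs L. The candidate substitutes are:
  - Poisson AIC, which acts as if φ = 1;
  - QAIC = −2 log L(Poisson) / φ̂ + 2k, with φ̂ from the cubic model;
  - the AIC of the Gaussian working model.

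**Why the substitute matters.** Poisson AIC accepts one extra term when the deviance falls by more than 2. With no true curve that fall behaves roughly as φ × χ²(1), so the chance of preferring quadratic to linear is about P(χ²(1) > 2/φ):
- φ = 1: P(χ²(1) > 2) ≈ 0.157.
- φ = 1 − 0.55 = 0.45 (binomial feeding counts): P(χ²(1) > 4.44) ≈ 0.035.

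In simulation, a curve (quadratic or cubic) was chosen in 4% of null binomial feeding series by Poisson AIC and in 23% by QAIC.

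**Step test, two-sided, nominal 0.05** (8,000 null series per row; Monte Carlo SE 0.0024 at 0.05 and 0.0034 at 0.10):

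| Scenario | Linear fixed | Poisson AIC | QAIC | Working-model AIC |
|---|---|---|---|---|
| Feeding, binomial variance (φ ≈ 0.45) | 0.046 | 0.065 | 0.101 | 0.102 |
| Feeding, Poisson variance | 0.049 | 0.099 | 0.101 | 0.101 |
| Feeding, φ ≈ 1.5 | 0.051 | 0.106 | 0.103 | 0.103 |
| NEC 7% | 0.045 | 0.093 | 0.095 | 0.087 |
| Severe NEC, assumed 3% | 0.040 | 0.070 | 0.072 | 0.056 |

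Ratios to the fixed form, by Poisson AIC:
- binomial feeding 0.065 / 0.046 ≈ 1.4;
- Poisson-variance feeding 0.099 / 0.049 ≈ 2.0;
- NEC 7% 0.093 / 0.045 ≈ 2.1;
- severe NEC 0.070 / 0.040 ≈ 1.75.

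Repeat simulations of the same design gave 0.071–0.072 (Poisson AIC) and 0.106–0.110 (QAIC) for binomial feeding.

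**Where the excess comes from.** In one equidispersed run the shares selected were linear 0.798, quadratic 0.122 and cubic 0.080, with step rejection rates of 0.050, 0.198 and 0.358 within each. The total is 0.798 × 0.050 + 0.122 × 0.198 + 0.080 × 0.358 = 0.040 + 0.024 + 0.029 ≈ 0.093. The linear share behaves as it should, and the excess arises where a curve was picked.

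**Bonferroni.** With five outcomes (divisor assumed), 0.05 / 5 = 0.01. At that level the fixed form gives 0.006–0.010 and the selected form 0.013–0.024, so the relative inflation remains.

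**Precision.** In an 80 + 9 month design the standard error of the step rises about 1.7-fold with a quadratic and 2.8-fold with a cubic.

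**The case against.** Several objections have force.

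- **The link is not stated.** The article defines the step and linear slope change first, then says curvature will also be assessed, with a caution about nine months. This can be read as a supplementary look that leaves the step-plus-slope result in place. Replacement by the lowest-AIC model is the more natural reading, but only implied. This stands, so the inflation is conditional.
- **Doubling is not general.** A reader might infer that the error doubles for every primary outcome. It does not. With Poisson AIC on binomial feeding counts the factor is about 1.4; for severe NEC at an assumed 3% it is 1.4 to 1.8.
- **Frequent false curves.** With over-dispersed NEC counts, Poisson AIC picks a curve in about 40% of null series, but only under an assumed monthly coefficient of variation of 0.5. The article says monthly variability is considerable and gives no value, so this is a stress case.
- **The undefined criterion is not the main source of the numerical damage.** Working-model AIC and QAIC behave almost alike for feeding. The inflation comes from selecting and then testing.
- **Autocorrelation terms.** Choosing them from correlation plots and an information criterion is conventional, and no effect on error was simulated. The article does not support a claim of harm there.
- **A later analysis plan may settle it.** It may, but the article positively names AIC alongside a model that has none. That pairing is a stated choice rather than an omitted detail.

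**Conclusion.** The pairing of a quasi-Poisson model with AIC is wrong as written, both for the trend shape and for the AR/MA terms: the rule has no defined meaning until a substitute is named. If the selected model supplies the reported step effect, its type I error at nominal 5% is about 7–11%, roughly 1.4 to 2 times nominal. One simulated case fell below that range: working-model AIC for severe NEC at an assumed 3%, at 0.056 against 0.040 with the linear form fixed. The Bonferroni correction does not address this, and the article does not say that the 95% intervals are adjusted.

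The size rests on the simulation assumptions listed above and on the implied link between AIC choice and the reported step. The documents do not support saying that the error doubles throughout, that the primary model is certainly chosen this way, or that the AR/MA choice biases the result. The AR/MA part is a correction of wording only.

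**What to change.** 1. State that the primary evaluation-phase form, for every outcome, is a step plus a linear slope change.
2. Report quadratic and cubic fits only as descriptive sensitivity analyses that do not replace the primary step estimate or its confidence interval.
3. Where an information criterion is kept for secondary comparison, including of AR/MA terms, name one defined for the fitted model: QAIC with a single common dispersion, or AIC from a full-likelihood binomial or negative binomial model. QAIC does not substitute for item 1: with selection left in place it still gave about 0.10 for feeding and 0.095 for NEC at 7%. With the linear form fixed, the error was 0.040–0.051.

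The cost is analysis wording, with no change to data collection. The downside is that a truly curved nine-month response would be described rather than tested, and the article already says its ability to detect one is limited.
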